### Control of bias

For the primary outcome of EMS call rate, we will collect at least 1 year of data before the intervention starts and also use a parallel design (for pairwise analysis) to examine the possible effect of seasonality. For the HABiT, participants will not be informed about the group comparisons. Surveys will be anonymous to decrease the possibility of social desirability bias.

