### Secondary questions

Will there be a *difference in the health perceptions, behaviours, intentions regarding behaviours, health literacy and knowledge of resources* in senior residents living in subsidised seniors’ housing after receiving the CHAP-EMS programme compared to their own baseline measurement, and compared to seniors in a building not receiving the programme?*Will there be a difference in health-seeking behaviour (eg, number of hospital emergency room visits and primary care visits)* by senior residents living in subsidised seniors’ housing compared to baseline, and compared to seniors in a building not receiving the programme?

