### Primary and secondary outcome measures

The primary outcome of EMS call rate (number of calls for building made by residents aged 55 years or older per 100 residents aged 55 years or older in the subsidised seniors’ building) will be available for each building from the EMS administrative database. The primary outcomes of change in measured systolic and diastolic BP, and difference in 10-year diabetes risk (CANRISK score), will be available from the measurements entered by the paramedics into the study database. The secondary outcomes will be difference in health perceptions, behaviours, intentions regarding behaviours, health literacy and knowledge of resources, measured by interviewer-led survey preintervention and postintervention; and difference in health-seeking behaviour (eg, number of ED visits/population 55 years and older), which will be based on administrative databases.

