### Data gathering procedures

Rates of EMS calls, ED visits, primary care visits and other healthcare utilisation will be collected from the administrative database of the local paramedic services, hospital ED databases, Institute for Clinical Evaluative Sciences (ICES) databases, the CHAP-EMS database and consenting participants’ primary care charts. Administrative data will be collected preintervention and postintervention, and retrospectively for the 12 months of intervention.

Health perceptions, behaviours and intentions regarding behaviours, health literacy and knowledge of resources related to chronic disease risk factors will be collected from consenting participants using an interviewer-led survey called the Health Awareness and Behaviour Tool (HABiT). This questionnaire covers the following domains: demographics, health status and quality of life, knowledge and risk factors (cardiovascular and diabetes), health utilisation and access to healthcare, and perceived concern and understanding of risk. It was developed by the research team, loosely based on existing validated questions. It has been pretested, piloted and validated in a sample of older adults in Ontario. Each item will be assigned a score and participant questionnaire results will be summarised as numerical scores. These outcomes will be analysed at the individual level and linked to administrative databases.

There will be two periods of data collection with the HABiT survey: a preintervention survey for residents of the intervention and control buildings administered up to 3 months prior to the intervention, and a postintervention survey administered up to 3 months immediately postintervention. Residents will be notified about the surveys through presentations at tenant engagement meetings, word-of-mouth and posters within the buildings. Surveys will be administered by trained college/university students and research assistants.

Physical measures (eg, BP, weight), risk assessment scores and process outcomes will be collected through the CHAP-EMS electronic database. The database is encrypted, and only accessible to the research team and the paramedics implementing the study.

Any urgent medical concerns identified or similar adverse events will be handled following protocol (eg, phoning the primary physician or EMS, depending on the level of urgency); these events will be recorded and reported to the ethics committee where appropriate.

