### Data analysis

We will use an intention-to-treat analysis and generalised estimating equations (GEE) assuming a Poisson distribution and an exchangeable correlation structure within a building to evaluate healthcare utilisation, BP and risk assessment scores, as well as to identify factors contributing to these outcomes. Rate of EMS calls will be analysed at the building-level only, using GEE. We will perform pairwise comparisons of outcomes for each month during the preintervention and intervention periods. We will identify trends in the outcomes during the preintervention and postintervention observation periods. Subgroup analysis by clusters (each building) and by location will be performed. The HABiT survey data will be summarised as a numerical score representing the participants’ perceptions and behaviours regarding CVD and diabetes, and analysed with GEEs. The intracluster correlation coefficient (ICC) will be computed to determine the effect of clustering (by the building the participants reside in) on the participants’ scores. Other outcomes will be analysed using descriptive statistics.

All analyses requiring health administrative data will be performed in a two-step process. First, CHAP-EMS data with identifiers will be securely transferred to ICES for health record linkage, as per the participant consent form. Once linked, the data set will be de-identified for subsequent analysis. All analyses will be performed using SPSS V.20. Statistical significance will be set at α=0.05 and adjusted using the Bonferroni method for secondary analyses. Results will be reported as rate ratios, 95% CIs and associated p values.

Twice a month, the CHAP-EMS data will be reviewed and analysed to assess for errors in data entry, and assure fidelity to the planned intervention (eg, monitor referral patterns by EMS personnel and proper use of the screening tools). This trial did not warrant formal externally managed data monitoring, or a formal committee, due to its minimal risks. Instead, interim analysis will be conducted on the process measures to evaluate intervention recruitment and implementation, and to provide regular reports to local stakeholders (eg, EMS, public health, local housing). Collaborative research agreements with local partners (eg, housing) specify that aggregate data will be shared with these local stakeholders. Individual data will not be released without written permission from the participant.

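### The HABiT surveys are declared anonymous, yet their outcomes are to be linked to administrative records and compared with residents' own baseline; the sections need reconciling

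*Protocol article*

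**What the plan says.** Five parts of the protocol article bear on the HABiT survey.

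- **Control of bias**, directly after a sentence on the HABiT: "Surveys will be anonymous to decrease the possibility of social desirability bias".
- **Data gathering procedures**: "There will be two periods of data collection with the HABiT survey", one before and one after the intervention, in both intervention and control buildings. On the resulting outcomes: "These outcomes will be analysed at the individual level and linked to administrative databases".
- **Secondary questions**: the first question asks about health perceptions, behaviours and related outcomes "compared to their own baseline measurement, and compared to seniors in a building not receiving the programme".
- **Data analysis**, on analyses that need health administrative data: "CHAP-EMS data with identifiers will be securely transferred to ICES for health record linkage, as per the participant consent form". Then: "Once linked, the data set will be de-identified for subsequent analysis".
- **Recruitment process**: in the control buildings, the researchers' sole contact with residents is to collect the survey at the start and end of the study.

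Under Primary and secondary outcome measures, the HABiT outcomes are "measured by interviewer-led survey preintervention and postintervention". The Ethics and dissemination section adds that every participant gives written consent.

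**The concern.** A survey that is anonymous when collected carries nothing that ties it to a person. It cannot be joined to that person's health record. Unless respondents supply some matching code, it cannot be joined to their second survey either. The article promises anonymity as a bias control and also plans analyses that depend on knowing who answered.

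At stake are the within-person reading of the first secondary question and every analysis that joins a HABiT score to administrative data. Timing makes this more than an editorial matter: if baseline surveys are collected without an identifier and without consent for linkage, neither can be restored afterwards.

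**Working it through.** The article gives no figure on this point, so the check compares the sections.

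**Step 1: what linkage requires.** Data analysis transfers data with identifiers and removes them only after linkage. Identifiers must therefore exist at collection. Data gathering procedures places HABiT outcomes among the data to be linked. Control of bias says those surveys carry no identity. These statements cannot all hold, at any sample size.

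**Step 2: what own-baseline comparison requires.** Read per person, it needs the two waves matched. A self-generated code could do this without names, so anonymity does not rule out matching in principle. The article mentions no such code, ID log or key.

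**Step 3: the two arms.**

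| | Intervention buildings | Control buildings |
|---|---|---|
| Identified research record outside the survey | Yes, for residents who attend sessions | None; the survey is the only contact |
| Anonymous HABiT linked to health records | Not possible | Not possible |
| Anonymous HABiT matched across waves | Not without a code | Not without a code |
| HABiT compared by building and wave | Possible | Possible |

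**Step 4: what does not depend on survey identity.**
- The EMS call rate comes from the EMS database and is analysed by building.
- Blood pressure and CANRISK come from the study database filled in by paramedics.
- The example utilisation measure under Primary and secondary outcome measures is emergency department visits relative to the population aged 55 or over, from administrative sources. On its face it needs no survey respondent.
- The planned GEE for HABiT uses building as the cluster, so it can be run on two unmatched waves that record only building and arm.

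**Step 5: illustration of the precision lost if waves are unmatched.** Let s² be the variance at each wave, n the respondents per wave and r the correlation between one person's two scores.
- Matched: variance of mean change = 2s²(1 − r)/n
- Unmatched: variance of mean change = 2s²/n
- Ratio = 1/(1 − r)

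The article gives no r, so these values are assumed:
- r = 0.3: 1/0.7 ≈ 1.4
- r = 0.5: 1/0.5 = 2
- r = 0.7: 1/0.3 ≈ 3.3

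The formula assumes equal variances, that everyone answers both times, and no clustering. With the same buildings surveyed twice, a stable building effect cancels even when persons are unmatched, so the ratio cannot be applied to total variance. It shows direction and rough scale only.

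**The case against.** The strongest defence is that the word anonymous was used loosely for confidential, or for de-identified before analysis. Written consent and the removal of identifiers after linkage both point that way. This is plausible, but it does not rescue the text. Anonymity is offered there as a means of reducing social desirability bias, and de-identification after linkage cannot affect how someone answers an interviewer. If only confidentiality was meant, the sentence needs correcting.

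A second defence is that no section prescribes a matched-pair analysis, and that own baseline, said of residents in the plural, can be read at group level. That stands as a possible reading. It softens the matching problem and leaves the linkage problem untouched.

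A reader might also infer three stronger things that the article does not support:

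- **That both secondary questions go unanswered.** The first also asks for a comparison with control buildings, which anonymous surveys still allow. The second concerns health-seeking behaviour, whose example measure is a population rate from administrative data.
- **That record linkage covers only residents who attend the programme.** The text speaks of CHAP-EMS data, and the article uses that name for the trial as well as for the programme and its database. The phrase is ambiguous.
- **That matching the two waves is impossible.** Only record linkage is strictly ruled out. Matching lacks a described device.

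**Conclusion.** The contradiction is real and lies in the current text. Control of bias cannot be carried out together with the linkage set out in Data gathering procedures and Data analysis. With no matching code described, it also conflicts with a per-person reading of the first secondary question. HABiT-to-record linkage is lost in both arms, and the control arm has no alternative research source of identifiers.

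The scope is limited to secondary survey outcomes: within-person HABiT change and HABiT analyses linked to administrative data. The size cannot be given as a figure, because the article states neither a HABiT correlation nor an expected re-response. The conclusion assumes that anonymous carries its ordinary meaning of no identity recorded at collection.

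**What to change.** **Preferred change.** Under Control of bias, describe the surveys as confidential and coded instead of anonymous. Then:

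1. Assign each respondent a study ID at the baseline survey, in both arms.
2. Obtain consent for record linkage at that point, in both arms.
3. Let only the research team hold the key.
4. Use the ID for the pre-post HABiT analysis and for joining HABiT to administrative data.
5. Leave the population-based utilisation rates as they are. Restricting them to survey respondents would narrow that outcome for no gain.

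**Cost.** An ethics-approved change to the survey consent wording and an ID log. Protection against social desirability bias becomes slightly weaker, but it is already limited because an interviewer conducts the survey.

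**Alternative.** If true anonymity matters more, keep it. Remove the own-baseline HABiT comparison from Secondary questions and the linked HABiT analysis from Data gathering procedures, and analyse the two waves as repeated cross-sections within buildings. The cost is the loss of within-person change and of any linked survey result.

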### Loss to follow-up

We do not expect a loss to follow-up (due to death or transfer of residence) of more than 5%, since this is a 1-year intervention study. Yearly death rates for males and females are 5.85 and 5.59 per 1000,^29^ which is unlikely to affect our study, despite the possibility of slightly higher rates due to the socioeconomic status of the study population.

## Ethics and dissemination

Following the Tri-Council Policy Statement, second edition,^30^ participation in this study is voluntary and all participants will provide written informed consent. Participants are able to withdraw at any point. Any protocol changes will be reviewed by the Hamilton Integrated Research Ethics Board and updated on the clinicaltrials.gov registry.

The study findings will be shared with the stakeholders in each community (eg, public health, community housing and emergency medical services), published in peer-reviewed journals and presented at conferences. Authorship will follow the criteria recommended by the International Committee of Medical Journal Editors.

## Discussion

This study will represent one of the first rigorous evaluations of community interventions across Ontario, within Canada and North America, using community paramedics and utilising a health promotion approach for cardiovascular risk; the study will try to ascertain changes in outcomes of lifestyle and health behaviour. Although the BP and cardiovascular screening of CHAP has been implemented and tested in small to mid-sized communities across Ontario,^21^ it has not been tested in this scenario of hard-to-reach seniors, with these outcomes, and using accommodated paramedics to assist with data collection, assessment, education and links to community resources, in the format of the CHAP-EMS programme. The strengths of this study include the use of a randomised controlled design, the adaptation and reconstitution of an intervention already demonstrated to reduce hospitalisations for cardiovascular disease, a pragmatic approach so as to generate findings regarding the effectiveness of the intervention that would be most applicable to real world clinical practice and policy, the delivery of the intervention in multiple communities each with their own context and the repositioning of healthcare resources (paramedics) to better maximise their skills and knowledge of the communities they serve. Applying the Precis-2 score,^31^ which is a measure of the pragmatic nature of a trial in a real-world setting, of 9 domains and a maximum score of 45, the CHAP-EMS protocol scored 41, indicating a pragmatic and useful approach. In more detail, the Precis-2 score considers the following elements as they are applied in the CHAP-EMS RCT as follows: eligibility—participants are those inhabiting seniors’ buildings and will be part of usual care (score 5); recruitment—not much extra effort is made to recruit participants over and above that which would be used in the usual care setting (score 5); setting—a very pragmatic choice of setting is utilised (score 5); organisation—resources utilised are those of the EMS service, and the organisation of care delivery in the intervention arm needs coordination (score 3); flexibility (delivery)—a fairly pragmatic choice with slight flexibility to usual care (score 3); flexibility (adherence)—a very pragmatic choice involving no more than usual encouragement to adhere to the intervention (score 5); follow-up—no more than usual follow-up (score 5); primary outcome—the outcome is of obvious importance to participants (score 5); and primary analysis—using intention to treat with all available data (score 5).

One limitation of our approach is that not every location will have subsidised housing buildings containing a majority of seniors, which will limit the generalisability of our findings. However, in Canada, this setting is sufficiently common, and that is critical in testing this strategy. Also, the study is focused on more urban areas with a large population of seniors living within a certain locale, and therefore the results will be limited to similar settings.

With our team's experience in implementing and evaluating the CHAP trial, we believe that expanding the programme to serve seniors living in subsidised housing, adding diabetes and falls screening and utilising accommodated paramedic personnel to run the programme, will be effective in lowering rates of EMS calls and ED visits through increasing risk factor detection and awareness, health education and referral to appropriate services. The relative decrease in EMS calls and ED visits will have implications in terms of healthcare savings. At the current time, real findings of this nature are not available and we need more research to understand what is clinically and policy-wise relevant. We also believe that the programme can improve the health behaviour of building occupants, which is expected to improve health outcomes. Such findings will have significant policy implications in favour of its widespread implementation. This study is in keeping with Canada's *Living Longer, Living Well* strategy^32^ for utilising allied health professionals more appropriately and extending their roles within health promotion and disease prevention. It addresses the question of the effectiveness of a novel form of health services delivery on healthcare processes, health outcomes and health resource utilisation.
